### Recruitment and procedure

Participants are recruited via advertisements through the Danish Student Counselling Service and their website (www.srg.dk) with a link to our trial website. Our trial website contains information about the trial and a Contact Form for prospective trial participants. People visiting our trial website are asked to answer three screening questions from the Improving Access to Psychological Therapies (IAPT) Phobia Scale about how much they would avoid three different anxiety-provoking situations [27]. People who screen positive for a minimum of one of the three anxiety symptoms on the IAPT Phobia Scale are invited to sign up for an initial interview. A psychologist (the support person for FearFighter™) conducts the initial interview face-to-face (see Table 1 for an overview). Danish Regional Ethical Committee-approved written information about the trial is presented to interested people alongside with information about alternative places to receive advice and treatment for their anxiety. The interested people are advised not to participate in the trial if they need help urgently or if they consider the duration of the trial to be too long. The people are subsequently assessed with the use of the MINI and the Standardised Assessment of Personality Abbreviated Scale (SAPAS). The MINI is a diagnostic instrument for major axis I psychiatric disorders and is used to identify people with an anxiety disorder and the presence of comorbidity. As the MINI does not identify or screen for personality disorders, the SAPAS is used as a screening instrument [28]. The SAPAS will only be used for background information to indicate the possible presence of comorbid personality disorders in a person. People will be eligible as participants if they comply with the inclusion and exclusion criteria. If a person gives their written informed consent to become a participant in the trial they will be randomised. All people are informed that they may withdraw their consent at any time during the trial.

**Table 1 Tab1:** Assessment tests and times of data collection in the FearFighter™ feasibility trial

Name of test	Screening/ website	Initial trial interview (week 0)	During trial	End-of-trial interview (week 10)	Follow-up (week 37)
Phobia Scale^a^	Xe		Xe		
Sociodemographic data		Xp			
Mini International Neuropsychiatric Interview		Xp		Xp	Xp
Standardised Assessment of Personality Abbreviated Scale		Xp			
Beck Anxiety Inventory		Xe		Xe	Xe
Symptom Checklist-90-R		Xe		Xe	Xe
WHO Well-Being Index		Xe		Xe	Xe
Sheehan Disability Scale		Xe		Xe	Xe
Adverse events			Xp	Xp	
Behaviour log			Xe		

*Xe* electronic collection of data, *Xp* paper collection of data

*WHO* World Health Organisation

^a^Improving Access to Psychological Therapies

### Data collection

Table 1 gives an overview of assessment tests and the time of data collection.

### Interventions

The participants in the experimental group receive Internet-based therapy using the programme FearFighter™ developed by [name] from the Maudsley Psychiatric Hospital in England [29]. FearFighter™ is a commercial online programme for the treatment of panic and phobia [30]. A Danish version of the programme was developed in 2013 [19]. The FearFighter™ programme is based on principles derived from CBT. The programme aims to teach people how to tackle negative thoughts and to challenge avoidance behaviours due to anxiety disorders. Participants receive an email with a link and an activation code for FearFighter™ as well as an empty ring binder to organise printed documents and session summaries from FearFighter™.

FearFighter™ consists of nine sessions. In each session a video-filmed therapist gives psychoeducation and explains the rationale for the training, followed by a number of exercises and tasks for homework. A whole week is assigned to do the homework. Homework is done between each session, and it is estimated to take 1 to 3 h, depending on the invested effort by the individual. Each on-line session excluding the homework takes about 30 to 40 min. The content of the nine sessions is described below.

#### Session 1

This consists of psychoeducation about CBT for anxiety, and the programme. The homework is to find a person who can encourage the patient to complete the sessions in the programme.

#### Session 2

This consists of psychoeducation about anxiety symptoms and safety behaviour. The homework is to register episodes of anxiety in an electronic diary built within the programme.

#### Session 3

This consists of psychoeducation about panic disorder and interoceptive exposure. Demonstration of three interoceptive exercises: flash cards, progressive relaxation, and applied tension. The homework is to do one or more of the exercises on a daily basis.

#### Session 4

This consists of psychoeducation about automatic negative thoughts. The homework is to challenge the negative thoughts with rational questions and to write answers and thoughts in a schema.

#### Session 5

This consists of psychoeducation about core beliefs about oneself. The homework is to challenge the negative core beliefs with rational questions and to try to replace them with positive core beliefs.

#### Session 6

This consists of psychoeducation about exposure and the hierarchy model of anxiety-provoking situations. The homework is to make a hierarchy of anxiety-provoking situations including goal setting.

#### Session 7

This consists of psychoeducation about how to prepare for exposure by pictures, sounds, and video. The homework is to prepare the exposure plan.

#### Session 8

This consists of support for the patient in the exposure exercises. The exposure exercises have to be repeated until the patient fulfils their exposure plan and goal setting.

#### Session 9

This session involves summing-up and counselling on how to master setbacks and prevent relapse and suggests continuing exposure exercises if necessary.

Between the sessions the programme will ask the person to indicate how bothered they are by their symptoms. The programme uses five brief questionnaires from IAPT about: (1) depression, (2) generalised anxiety, (3) phobia, (4) work and social adjustment, and (5) self-harm. The system gives feedback to the participant, showing a graph on treatment progress. In all, the FearFighter™ programme recommends that participants spend 5 to 8 h with the FearFighter™ programme and spend 32 to 35 h practising the assignments and exposure exercises.

### Support person and support manual

Each trial participant is contacted over the telephone by a support person once a week during the 9 weeks of intervention. Each telephone contact should take about 10 min and a maximum of 1.5 h for the whole intervention period. The purpose of the contact is to secure and assess compliance and also to assist the participant’s adherence to the programme. The support person follows a support manual for the amount, type, and content of the support given. The support person must not engage in a psychotherapeutic dialogue with the participants. The support person who performs all the initial interviews and baseline assessments will also support the 32 participants in the experimental group. The reason for this is to optimise the alliance between the participants and the support person.

The manual for the support person prepared by the company behind the Danish version of FearFighter™ was tested by us, the trial investigators, and found to be too unspecific and vague for having standardised support in our trial. Therefore, we prepared our own manual with specific instructions for the support at each session in FearFighter™. None of the instructions in our manual are in conflict with, or violate the general instructions in, the support manual by the Danish company. Both the original support manual and our manual are written in Danish and can be obtained upon request.

## Outcomes

### Feasibility outcomes

The primary feasibility outcome is the proportion of randomised participants out of all eligible people. Eligible participants are those who fulfil our inclusion criteria. The secondary feasibility outcome is compliance, defined as the number of participants completing at least six of the nine planned FearFighter™ sessions in the experimental group. FearFighter™ will automatically register time for login and save the exercises that have been completed. The support person sees a tracking log on the administration webpage for FearFighter™ for each participant and the compliance will be assessed during the weekly telephone calls with the experimental participants and summed-up at the end of the trial interview.

Participants who complete six or more sessions in FearFighter™ but who fail to show up for post-treatment assessment are still regarded as completers in the feasibility outcome. If the participants complete less than six sessions they will be regarded as noncompleters (dropouts).

### Exploratory clinical outcomes

The primary exploratory clinical outcome is the proportion of participants who no longer fulfil the diagnostic criteria for an anxiety disorder at the end of the intervention as assessed with the MINI [26]. Other exploratory clinical outcomes are severity of psychiatric symptoms, disability, and well-being measured using the following described participant-reported instruments: the Beck Anxiety Inventory (BAI) is a 21-item general questionnaire for anxiety symptoms during the last 14 days rated on a 4-point Likert scale from 0 to 3. The maximum score is 63. A score of 26 or greater indicates severe anxiety [31]. The Symptom Checklist-90 revised (SCL-90-R) is a 90-item multidimensional questionnaire measuring psychopathology and psychological distress during the last 7 days on nine primary symptom dimensions and three global dimensions. Each item is rated on a 5-point Likert scale from 0 to 4. The score on each dimension is the mean of the included items [32]. The Global Severity Index (GSI), interpersonal sensitivity dimension (IS), anxiety dimension (ANX), and phobic anxiety dimension (PHOB) are used in this trial. The SCL-90-R is a valid and reliable outcome, used often in psychotherapy research, and Danish norms are available [33]. The Sheehan Disability Scale (SDS) is a 3-item questionnaire for occupational function, social function, and family function rated on an 11-point Likert scale. Specific scoring for the three functions is from 0 to 10 and a global score for the general function is from 0 to 30. A score of 5 or greater on the specific scales indicates dysfunction [34]. The WHO Well-Being Index is a 5-item questionnaire for the assessment of health-related quality of life for the last 14 days on a 6-point Likert scale from 0 to 5. Scores are summated, with raw scores ranging from 0 to 25 [35].

Serious adverse events and other untoward events that require hospitalisation, are life-threatening, or result in death are collected following the SPIRIT recommendations [20]. All adverse and untoward events will be categorised and summated. Finally, the proportion in the groups of experimental and control participants who are compliant with the randomised intervention, defined as the lack of any psychological treatment during the 9-week intervention period, will be registered. At follow-up, it will be registered if participants have been engaged in psychological treatment since the end of the trial, although no restrictions will be imposed on the participants during the follow-up period.

All scores will be compared between the two groups at post-treatment (week 10) and at follow-up (week 37). Serious adverse events and other untoward events will be gathered during the intervention for the intervention group and at post-treatment for both the control and the intervention groups.

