**Methods and design:**

We will conduct an investigator-initiated, feasibility randomised controlled trial. Sixty-four participants are expected to be recruited via an advertisement posted on the homepage of the Student Counselling Service in Denmark. The inclusion criterion for participation in the trial will be the presence of anxiety disorder as assessed with the Mini International Neuropsychiatric Interview. The exclusion criteria will be suicidal risk, an ongoing episode of bipolar disorder or psychosis, concurrent psychological treatment for the anxiety disorder, considered unable to attend the intervention as planned (due to vacation, work/study placement, sickness, or similar occurrences), or lack of informed consent. The intervention group will be offered nine sessions with the ICBT programme FearFighter™ and a weekly telephone contact to support compliance. The control group will receive no intervention. We define the feasibility outcomes as follows: the fraction of randomised participants out of the eligible people (the lower 95 % confidence interval (CI) ≥ 50 %); and the fraction of compliant participants (those receiving at least six out of nine sessions) in the intervention group (the lower 95 % CI ≥ 60 %). The exploratory clinical outcomes are the number of participants no longer meeting the diagnostic criteria for an anxiety disorder at the end of the trial and level of distress (Beck Anxiety Inventory, Symptom Checklist-90-R, WHO Well-Being Index, Sheehan Disability Scale); the number of severe adverse events; and the occurrence of any psychological treatment outside the trial.

To prevent bias in design, and in the gathering and analysis of data throughout the trial, we will follow the SPIRIT 2013 statement which defines standard protocol items for clinical trials.

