Number of participants complying at least 6/9 FearFighter™ sessions/ randomised participants	Not relevant	Proportion	Test analogous to the above feasibility outcome with the difference that now we want to secure that the sample is not from a population being less than 60 % compliant
Exploratory outcome			
Number of participants who no longer fulfil the diagnostic criteria for an anxiety disorder	MINI	Proportion	Fisher’s exact test and logistic regression adjusted by the protocol-specified stratification variable (the result of the latter test is the primary of the 2 tests)
Severity of anxiety	BAI	Continuous	The general linear univariate model (GLM) taking stratification variables and baseline BAI into account
Psychological distress and psychopathology	SCL-90-R	Continuous	GLM taking stratification variables and baseline SCL-90-R into account
Positive well-being	WHO-5	Ordinal	The proportional odds model for ordinal response taking stratification variables and baseline WHO-5 into account (if conditions are not fulfilled, then nonparametric Mann-Whitney)
Functional impairment	SDS	Continuous	GLM taking stratification variables and baseline SDS into account.
Number of randomised receiving psychological treatment during the 9 weeks	Interview	Proportion	Fisher’s exact test and logistic regression adjusted by the protocol-specified stratification variable (the result of the latter test is the primary of the 2 tests).
Number of participants with one or more adverse event	Interview	Proportion	Fisher’s exact test and logistic regression adjusted by the protocol-specified stratification variable (the result of the latter test is the primary of the 2 tests)

*BAI* Beck Anxiety Inventory, *MINI* Mini International Neuropsychiatric Interview*, SCL-90-R* Symptom Checklist-90 revised, *SDS* Sheehan Disability Scale, *WHO* World Health Organisation

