We have added one additional exploratory outcome, namely the proportion of participants in the experimental and control groups who are compliant with the randomised intervention, defined as the absence of any psychological treatment during the 9-week intervention period. This outcome, as well as the proportion of participants experiencing an adverse event, will be analysed as the other exploratory outcomes with Fisher’s exact test and logistic regression, adjusted by the protocol-specified stratification variable (the result of the latter test is the primary of the two tests). Adverse events will also be reported according to type, severity, and probable relation to the interventions for the two intervention groups.

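### The harm outcome has conflicting scopes and units (severe events, serious events, all events, participants with any event), so a serious-only count could end up reported as any adverse event

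*Protocol article*

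**What the plan says.** All of the following is in the protocol article.

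- **Abstract, Methods and design:** the harm outcome is "the number of severe adverse events".
- **Outcomes, Exploratory clinical outcomes, collection sentence:** "Serious adverse events and other untoward events that require hospitalisation, are life-threatening, or result in death are collected following the SPIRIT recommendations".
- **Same section, next sentence:** "All adverse and untoward events will be categorised and summated".
- **Same section, on timing:** "Serious adverse events and other untoward events will be gathered during the intervention for the intervention group and at post-treatment for both" groups. The limit to hospitalising, life-threatening or fatal events is not repeated here.
- **Table 1 (under Recruitment and procedure):** a row headed "Adverse events", on paper, during the trial and at week 10, with no limit on seriousness.
- **Table 2 (under Statistical analyses):** the tested outcome is "Number of participants with one or more adverse event", with interview as the source. Fisher's exact test and a stratification-adjusted logistic regression are planned, and the regression is primary.
- **Statistical analyses, text after Table 2:** "the proportion of participants experiencing an adverse event, will be analysed as the other exploratory outcomes", and "Adverse events will also be reported according to type, severity, and probable relation to the interventions for the two intervention groups".

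**The concern.** *Severe* grades the intensity of an event. *Serious* classifies it by consequence, such as admission, threat to life or death. *Any adverse event* covers both and everything below them. The article uses all three for what should be one outcome. It also changes the unit: events in the abstract and the summation sentence, participants in Table 2. The one sentence that says which kinds of event are collected is narrower than the row that is tested.

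The abstract gives the objective as a feasibility assessment of benefits and harms. Suppose interviewers follow the collection sentence and the analyst follows Table 2. A count of serious events would then appear under a label that promises all adverse events, and a row of zeros could be taken to show that the programme does no harm.

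**Working it through.** **1. No figure to reproduce.** The article states no event rate, effect size or power for the harm outcome. Its only sample-size figure, the confidence interval for the randomised fraction, does not bear on this point.

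**2. The versions side by side.** Take three hypothetical participants whose events have already been accepted as adverse events:

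- A has one moderate event, not serious.
- B has two severe events, neither serious.
- C has one event of moderate intensity that led to admission.

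| Version | A | B | C | Total |
|---|---|---|---|---|
| Abstract: severe events | 0 | 2 | 0 | 2 events |
| Collection sentence, read alone | 0 | 0 | 1 | 1 event |
| Summation sentence: all events | 1 | 2 | 1 | 4 events |
| Table 2: participants with any event | 1 | 1 | 1 | 3 participants |

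The same three people give four different totals. Reporting by severity, as the text after Table 2 plans, has little content unless events below the serious threshold were recorded.

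**3. Size if only serious events are collected.** From the article: 64 participants, 1:1 allocation, 32 per arm. The per-participant rate p over the 10 weeks is an assumption, with range 0.5 to 2 %.

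- Expected participants with an event per arm: 32 × p = 0.16 (0.5 %), 0.32 (1 %), 0.64 (2 %).
- Chance of no event in the trial: (1 − p)^64 = 73 %, 53 %, 27 %.
- Chance that at least one arm has none: 1 − [1 − (1 − p)^32]² = 98 %, 92 %, 77 %. With an empty arm the logistic regression named as primary has no finite odds ratio.
- Fisher's test, 32 v 32, two-sided, x v 0: p = 2 × C(32, x)/C(64, x). For x = 5, 2 × 201,376/7,624,512 = 0.053. For x = 6, 2 × 906,192/74,974,368 = 0.024. At least 6 v 0 is needed for p < 0.05.
- Zero of 32 has an exact upper 95 % limit of 1 − 0.025^(1/32) = 10.9 %, so an empty row is weak evidence even about serious events.

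**4. Size if all adverse events are collected.** At an assumed 20 to 40 % of participants, 32 × 0.20 = 6.4 to 32 × 0.40 = 12.8 are expected per arm. The gap from step 3 is at least 6.4/0.64 = 10-fold, but it depends on the two assumed ranges.

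**5. Unequal ascertainment.** Under the timing sentence, events are gathered during treatment in the intervention arm only. Suppose the true rates are equal but the extra contacts raise the recorded proportion from 20 to 40 % in that arm (an assumption). Fisher's test would then give p < 0.05 in about 33 % of trials. If all events are collected, pooling the two sources would therefore bias the Table 2 comparison.

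**The case against.** The strongest reply is that the collection sentence never says *only*. The next sentence covers all adverse and untoward events, the timing sentence drops the restriction, the Table 1 row has none, and the analysis text reports by severity. Most of the text thus points to broad collection, with one narrower sentence. This stands. A reader might infer that the tested endpoint must be either nearly empty or built on events that are not collected. The documents do not support that, because a third reading, in which all events are collected and tested, is open.

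A reader might also infer that lesser harms are never asked about. That goes too far as well. BAI, SCL-90-R, SDS and the WHO index measure worsening in both arms at weeks 10 and 37, and the programme asks treated participants about phobia, depression and self-harm between sessions. These do not replace adverse event recording, but they do ask about such problems.

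Nor does the article say whether panic provoked by exposure counts as an adverse event. Such operational definitions may be in the full protocol, so no example here relies on that.

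Finally, the event rates are assumed, and p values only select hypothesis-generating outcomes. Both are true and limit the weight of the point. They do not remove the conflict, which is between definitions that the article itself states.

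**Conclusion.** The scope and the unit of the harm outcome contradict each other across the abstract, Outcomes, Table 1, Table 2 and the analysis text, and the passages must be reconciled. This part rests on the wording alone.

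The consequence is conditional. If collection follows the collection sentence, the Table 2 row would carry a serious-only count under an any-event label, with a 27 to 73 % chance of no event among 64 people at assumed rates of 2 to 0.5 %. If all events were collected, the row is correctly labelled, and the remaining faults are the abstract's term, the mixed units and the unequal gathering between arms.

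The effect is on the harms part of the objective. The feasibility decision, which rests on randomisation and compliance, is not affected. The point should be corrected but is not critical.

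**What to change.** - Use one definition and one unit (participants with at least one event) in the abstract, Table 1, Outcomes, Table 2 and the analysis text. If *serious* is meant in the abstract, replace *severe* with it.
- State in Outcomes whether non-serious events are collected.
- **If they are:** base the between-group comparison in Table 2 on the week-10 interview, with the same question in both arms. Report events gathered during treatment in the intervention arm separately, and add participants with a serious adverse event as a descriptive line.
- **If only serious events were collected:** relabel the Table 2 row as serious adverse events and state that non-serious harms were not assessed.

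A broader question at existing contacts is not enough by itself, because the weekly calls are described for the intervention arm only. The Trial status section also expected post-treatment data by summer 2016, and the article appeared in October 2016. On that schedule the remedy is clarification, separate reporting or relabelling rather than new data collection.

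The cost is a few wording changes and slightly more coding of events or, with relabelling, a more limited harm claim.

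### No adverse events are collected between week 10 and week 37, although outcome scores are compared between the arms at week 37

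*Protocol article*

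**What the plan says.** Under Exploratory clinical outcomes, the protocol article sets the harms schedule: "Serious adverse events and other untoward events will be gathered during the intervention for the intervention group and at post-treatment for both" arms. In Table 1, under Recruitment and procedure, the row "Adverse events" is marked for the during-trial period and the week-10 interview, and the week-37 cell is empty. Text and table agree, so this is the planned schedule and not a slip in one place.

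Benefit runs on a longer clock. Table 1 repeats the MINI, BAI, SCL-90-R, WHO-5 and SDS at week 37, and the text says: "All scores will be compared between the two groups at post-treatment (week 10) and at follow-up (week 37"). The only other item named for follow-up is whether the participant has had psychological treatment since week 10.

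The Abstract gives feasibility assessment of both benefits and harms as the objective. Table 2 compares between arms the proportion of participants with at least one adverse event.

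On the programme itself, the Interventions section says of session 8: "The exposure exercises have to be repeated until the patient fulfils their exposure plan and goal setting". Session 9 "suggests continuing exposure exercises if necessary".

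**The concern.** The two sides of the stated objective are observed over different periods. A hospitalisation, a life-threatening event or a death between week 10 and week 37, in either arm, would enter no adverse event outcome, while the same participants' symptom scores would be compared at week 37. Anyone reading the follow-up results would have a benefit estimate with no harm data for the same period.

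The gap lies in data collection. An analysis plan cannot make up for events that nobody asked about, so this cannot be left to a later document. It has some relevance to this intervention because exposure comes late in the programme and may continue after the last session.

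**Working it through.** No sample size, power or alpha enters this point. The check compares schedules and hours.

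**1. Calendar time without collection** (Table 1; Exploratory clinical outcomes)

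- Last adverse event collection: week 10. Last score comparison: week 37.
- 37 − 10 = 27 weeks; 27/37 = 0.730, or 73%.

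**2. Can the week-37 scales stand in for it?** (look-back periods from Exploratory clinical outcomes)

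- BAI and WHO-5 cover the last 14 days, so 27 − 2 = 25 weeks of the gap are out of reach.
- SCL-90-R covers the last 7 days, so 27 − 1 = 26 weeks are out of reach.
- The MINI and SDS rate diagnosis and function. They would show lasting deterioration but do not record discrete events.

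**3. Does practice run past week 10?** (Interventions)

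Inputs: homework between sessions, of which the article says "it is estimated to take 1 to 3 h, depending on the invested effort by the individual", with one week per session; and the programme's recommendation to "spend 32 to 35 h practising the assignments and exposure exercises".

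Total homework = weeks × hours per week:

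- 8 gaps: 8 to 24 h
- 9 weeks: 9 to 27 h
- 10 weeks: 10 to 30 h

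None reaches 32 h, so the recommended total is not reproduced from the weekly load. Two readings are possible:

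- Keep the weekly load. 32 to 35 h then takes 32/3 = 10.7 to 35/3 = 11.7 weeks at 3 h, 16 to 17.5 weeks at 2 h, and 32 to 35 weeks at 1 h. Some practice falls after week 10.
- Keep the total and fit it into the intervention. The load is then 32/10 = 3.2 to 35/10 = 3.5 h a week over ten weeks, or 32/9 = 3.6 to 35/9 = 3.9 h over nine. Nothing falls after week 10.

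Share of exposure practice done by week 10 on the first reading, assuming a constant rate r, seven weeks of earlier homework and three weeks from session 8 to week 10: 3r/(T − 7r), with T = 32 to 35 h.

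- r = 1: 3/28 to 3/25 = 11% to 12%
- r = 2: 6/21 to 6/18 = 29% to 33%
- r = 3: 9/14 to 9/11 = 64% to 82%

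The share falling after week 10 is therefore anywhere from 0% (second reading) to about 89% (1 h a week, T = 35).

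**4. Why the repair must handle weeks 0 to 10 with care**

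The text gathers events during the intervention in the intervention arm only; controls are asked at week 10. Assume that both arms have the same true proportion t with an event, that capture is complete in the intervention arm, and that a fraction s is captured in controls. The apparent odds ratio is [t/(1 − t)] / [ts/(1 − ts)].

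- t = 0.10, s = 0.9: (0.10/0.90)/(0.09/0.91) = 1.12
- t = 0.30, s = 0.5: (0.30/0.70)/(0.15/0.85) = 2.43

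Both t and s are assumed, since the article gives no values. Over t = 0.10 to 0.30 and s = 0.5 to 0.9, the spurious odds ratio runs from about 1.1 to 2.4 against the intervention.

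**The case against.** The best defence is that harm is collected over the period that matters most here. The primary exploratory clinical outcome is remission at the end of the intervention, Table 1 labels week 10 the end-of-trial interview, and harm collection matches that time point. Success is judged on recruitment and compliance alone, and clinical p values serve only to pick hypotheses. After week 10 outside treatment is unrestricted, so later events would be hard to attribute. All of this is fair, and it lowers the weight of the point. It does not remove it: harms are part of the stated objective, and unrestricted outside treatment clouds the week-37 score comparison just as much, yet that comparison is planned.

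A reader might go further and infer that most harms of exposure go unseen. The documents do not support that. All nine sessions, including the hierarchy (6), preparation (7) and supported exposure (8), lie inside the nine-week intervention, when events are gathered in the intervention arm. Interoceptive exercises start as early as session 3. Continuing after session 9 is conditional on need. At 3 h a week most exposure practice is done by week 10, and if the full hours fit the intervention, all of it is.

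Nor is the gap wholly blind to harm, since the week-37 MINI and scales would show worsening that persists.

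**Conclusion.** The point holds in limited form. No adverse event collection is planned for 27 of the 37 weeks (73%), although scores are compared between arms at week 37, harms belong to the objective, and exposure may continue after the last session. This rests on the article's text and Table 1, which agree, and needs no assumption. The 73% is calendar time, not a share of treatment received.

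How much exposure practice falls after week 10 cannot be settled from the article: 0% to about 89%, depending on which hour figure is kept and on a constant weekly rate. The weekly and total hours contradict each other and must be reconciled, but they do not establish that most exposure comes after week 10.

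For an exploratory outcome in a 64-person feasibility trial, this is a worthwhile and inexpensive improvement, not a threat to the feasibility conclusions.

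**What to change.** - Add adverse events to the week-37 column of Table 1 and to the sentence on harms under Exploratory clinical outcomes, with the same question put to both arms at the existing week-37 interview.
- Report participants with an event in weeks 10 to 37 by arm, separately from weeks 0 to 10, next to the outside treatment already registered at follow-up.
- For weeks 0 to 10 and any overall comparison, base the between-arm test on events elicited by the identical week-10 (and week-37) question. Report events gathered during treatment in the intervention arm descriptively. Otherwise the unequal elicitation carries into the new totals.
- Reconcile the weekly homework estimate with the recommended total practice hours.

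The cost is one item on an interview that already takes place, one form, and a few lines of protocol text; sample size and type of test stay as they are. The drawback is recall over 27 weeks. It cannot be assumed equal: participants know their allocation, and only the intervention arm has had weekly contact and earlier event collection. Report the week 10 to 37 figures with that caveat.
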